# Evaluation of outcomes, costs, and feasibility of home-based geriatric rehabilitation after inpatient rehabilitation: study protocol of the “Better@Home” multicentre prospective cohort study with historical control group

**DOI:** 10.1186/s12877-025-06573-6

**Published:** 2025-11-28

**Keywords:** Geriatric rehabilitation, Home-based geriatric rehabilitation, Multicentre-prospective cohortstudy, Outcomes- costs-and feasibility

## Abstract

**Background:**

The increasing demands of an aging population, healthcare workforce shortages, financial constraints, and a shift in care perspectives call for rethinking geriatric rehabilitation (GR). To ensure GR remains sustainable, a transition towards home-based GR is proposed, reducing the need for prolonged inpatient GR. This study assesses the outcomes, costs and feasibility of the “Better@Home” program, in which home-based GR replaces part of inpatient GR.

**Methods:**

This multicenter cohort study is conducted in eight GR facilities in the Netherlands, implementing the Better@Home program. Core elements of this program include replacing part of inpatient GR with home-based GR, focusing on participation goals, using eHealth, promoting self-management, and fostering close collaboration among all care partners. Data is gathered through semi-structured interviews, questionnaires, group interviews, registration forms, and electronic patient files.

The Better@Home study is designed as a cohort study accompanied by a mixed-methods feasibility study. The study includes an outcome-and cost assessment. Within the cohort study, two evaluations can be distinguished. The first is a *comparative evaluation*, comparing the multicentre prospective Better@Home cohort with a historical control group on the primary outcome measure, as well as patient, family, and healthcare-related costs, from admission to completion of GR. The primary outcome measure of the *comparative evaluation* is independence in activities of daily living, assessed by the Barthel Index. The second is a *follow-up evaluation*, to assess the course of the outcomes and costs from GR admission to three months of follow-up after GR completion, solely in the Better@Home cohort. The primary outcome measure of the *follow-up evaluation* is participation, assessed by the Canadian Occupational Performance Measure. The *mixed-methods* feasibility study incorporates both quantitative and qualitative methods. It evaluates the program’s reach, performance according to plan, active engagement of patients and informal caregivers, barriers and facilitators affecting implementation, and the opinions of patients, informal caregivers, and professionals on the program.

**Discussion:**

This study offers insights into the potential of home-based GR. The multicentre and multilayered design enables a comprehensive evaluation of the Better@Home program’s outcomes, costs and feasibility, providing a basis for further optimization and upscaling of home-based GR.

**Supplementary Information:**

The online version contains supplementary material available at 10.1186/s12877-025-06573-6.

## Background

Due to population aging, shortages of healthcare professionals, pressures on healthcare budgets, and a shifting perspective on care, geriatric rehabilitation (GR) should be reconfigured [1–4]. GR is a multidimensional approach of diagnostic and therapeutic interventions to optimize functional capacity, promote activity, and preserve functional reserve and social participation in older people with disabling impairments [5].

To continue providing effective, affordable, and accessible GR for an increasing number of older people with a decreasing number of healthcare professionals, GR must be made future-proof. A crucial aspect of future-proof GR is providing ‘the right care in the right place’ through home-based rehabilitation after (shorter) inpatient rehabilitation, potentially with technological support [2]. First, this can contribute to a more efficient organization of care (e.g., reduced personnel and lower costs). Second, home-based GR is expected to positively affect older people because rehabilitation at home offers a realistic rehabilitation environment in which patients can practice their activities of daily living [6]. It is known that older adults often experience the transition from inpatient rehabilitation to home as very challenging [7]. After discharge, they truly realize the limitations they face in their homes. This manifests in a feeling of not being able to successfully continue their daily functioning and finding it challenging to organize meaningful participation in their home environment [7]. Home-based GR may help ease this transition because older adults can practice meaningful activities at home under the guidance of multidisciplinary GR professionals and with the assistance of (other) formal and informal caregivers. Sustainable strategies can be developed to resume life and remain at home longer despite experiencing limitations [8, 9].

Despite a broad consensus on the importance of home-based GR after (shorter) inpatient GR [5, 10], it is currently only used on a small scale in the Netherlands. There are various barriers, including regulatory and funding issues, and a lack of knowledge and skills to apply home-based GR in practice [11, 12]. There is insufficient understanding of how home-based GR after inpatient GR can be provided in a feasible and (cost-)effective way.

To overcome the barriers and challenges, we developed and implemented a home-based GR program in which home-based GR substitutes part of the inpatient GR. The program, called Better@Home, is based on current best practices in healthcare organizations in the Netherlands and results from previous research [13]. This includes knowledge on strengthening self-management skills and social networks through reablement [14, 15], the application of eHealth [16–18], and the development of care pathways [19, 20]. The core principles in the Better@Home program are: (1) replacing part of inpatient GR by home-based GR; (2) focusing on participation goals during both inpatient GR and home-based GR; (3) using eHealth to support rehabilitation; (4) promoting the patients’ self-management through the application of various reablement strategies; and (5) close collaboration between all care partners involved during the GR trajectory.

The aim of our study is to assess the outcomes, costs, and feasibility of home-based GR after shorter inpatient rehabilitation.

## Methods

### Study design

The Better@Home study is a cohort study accompanied by a mixed-methods feasibility study (Fig. 1). The Better@Home study includes an outcome assessment to assess the program’s outcomes and a cost assessment to assess the costs in relation to the outcomes. Within the cohort study, two evaluations can be distinguished: [1] a *comparative evaluation*, to assess the outcomes and costs from admission to completion of GR in the prospective Better@Home cohort receiving the Better@Home program, compared to a historical control group who received usual care; [2] a *follow-up evaluation*, to assess the course of the outcomes and costs solely within the prospective Better@Home cohort, from admission to three months post-GR. The *mixed-methods study* is to assess the feasibility of the Better@Home program, from admission to three months post-GR. The mixed-methods study incorporates both quantitative and qualitative methods. It evaluates the program’s reach, performance according to plan, active engagement of patients and informal caregivers, barriers and facilitators affecting implementation, and the opinions of patients, informal caregivers, and professionals on the program.

**Fig. 1 Fig1:**
[figure not shown]
Schematic overview of study designs and cohorts in the Better@Home study

The current study was assessed by the Medical Ethics Committee of University Hospital Maastricht/Maastricht University (reference number 2023–3744) (see Ethics declarations). Written informed consent was obtained from the participants in the Better@Home cohort (patients, informal caregivers, and care professionals who participated in the questionnaire and/or interview). All patients’ data in the Care as usual cohort is received from the GR facilities anonymized, so it cannot be linked to specific persons by the research team.

### Setting and population

The Better@Home study is performed in eight GR facilities situated in the Netherlands, embedded in three university networks for the care sector: Limburg Living lab in Ageing and Long-term Care (AWO-L) on behalf of Maastricht University; University Network of Organizations for Care for Older Adults (UNO Amsterdam) on behalf of Amsterdam University Medical Center (location VUmc); and University network for the Care Sector South-Holland (UNC-ZH) on behalf of University Leiden, in which these organizations participate. GR facilities have been invited to participate if they were willing to develop and implement the Better@Home program in their GR facility. This could be organizations with and without prior experience in providing home-based GR.

The target population for the prospective Better@Home cohort consists of patients admitted to one of the eight participating GR facilities that implemented the Better@Home program. Patients are eligible for participation in the Better@Home cohort if they meet the following inclusion criteria: (1) admitted to one of the eight participating GR facilities between December 2023 and November 2024; (2) are considered eligible for the Better@Home program as assessed by the multidisciplinary team of each GR facility individually (based on their physical, cognitive and psychological functioning); (3) are living in the community; (4) are able to participate in an interview as assessed by the multidisciplinary team of each GR facility individually (based on their physical, cognitive and psychological functioning); (5) are able to speak and understand Dutch; and (6) are able to provide informed consent. Furthermore, the multidisciplinary teams of each GR facility individually assess the eligibility of each patient on a combination of secondary criteria based on local GR facility protocols: (1) each GR facility is free to choose sub-population(s) based on diagnosis to be eligible for the program. This can be a single diagnosis group, several diagnosis groups, or all patients admitted to GR; (2) practical considerations (such as travel distance from the GR facility to the patient’s home and home hygiene status); and (3) patient-related considerations (such as availability of professional home care and informal care, functional status and wishes of the patient). In addition, the primary informal caregiver of every patient included in the Better@Home program will be invited to participate in the study. A person is considered the primary informal caregiver if the patient indicates that they are the person primarily involved in the informal care and support for this patient. For the informal caregivers, no historical control group is available.

The matched historical control group represents patients who received usual care. This cohort consists of patients admitted to the participating GR facilities between January 2022 and June 2023—at least six months before the implementation of the Better@Home program—thereby minimizing contamination bias while ensuring a similar context of care. Furthermore, in order to maintain the integrity of the comparison, patients who received home-based GR prior to the implementation of Better@Home program will be excluded from the matched historical control group. Several participating GR facilities already offered home-based GR during the comparison period; including these patients could lead to contamination of the usual care group and an underestimation of the Better@Home program’s effects.

Eligible patients for the Better@Home program will be invited individually by a multidisciplinary team member of each GR facility to participate in the study. The multidisciplinary team assesses eligibility within the first two weeks after admission to GR. After a patient indicates potential interest in participating in the study, a research team member contacts the patient to provide further detailed information on the study and check the inclusion criteria. Patients who agree to participate in the study are asked whether their primary informal caregiver can be approached for participation in the study. After obtaining the patient’s written consent, the informal caregiver is informed about the study and invited to participate.

### The Better@Home program

The Better@Home program is developed by the eight GR facilities participating in this study in collaboration with a learning network. The learning network includes project group members from the participating GR facilities (e.g., care professionals, managers, and policymakers), as well as (senior) researchers from the three university networks for the care sector. Moreover, representatives of national healthcare insurers, interest groups for older adult patients and informal caregivers, and other relevant stakeholders are also present in the learning network. The learning network facilitates the exchange of experiences and mutual learning across GR facilities.

A pilot project conducted by one of the eight participating GR facilities resulted in a draft version of the program, which led to the development of the final Better@Home program. The following five core components are present in the Better@Home program (Table 1): (1) Replacing part of inpatient GR by home-based GR; (2) Focusing on participation goals during GR; (3) Using eHealth to support rehabilitation; (4) Promoting patients’ self-management by applying Reablement strategies; and (5) Close collaboration between all relevant care partners involved in the GR trajectory. Each participating GR facility established a working group responsible for developing a site-specific, local Better@Home protocol containing the core components of the Better@Home program. While each of the five core components are mandatory, each GR facility retains the freedom to decide to what extent they implement each component in accordance with their local protocols. Each local Better@Home protocol is conducted by the multidisciplinary GR teams in each facility. In the Netherlands, these teams generally consist of physicians, nurses, physical-, occupational-, and speech therapists, dieticians, psychologists, and often complemented by social workers and nurse practitioners. The Better@Home program was gradually implemented between December 2023 and February 2024 and ended in November 2024.

**Table 1 Tab1:** Core components of the Better@Home program

Core components Better@Home intervention program
*1) Replacing part of inpatient GR by home-based GR* • Each GR facility strives to reduce the duration of the inpatient GR with an average of 5 to 7 days and to replace this by a period of home-based GR. • The length and intensity of the home-based GR can vary and is tailored to the needs of the patient. • The home-based GR should at least partly consist of therapy provided at the patients’ home and can be supplemented with outpatient therapy at the GR facility and/or remote therapy using eHealth.
*2) Focusing on participation goals during both inpatient GR and home-based GR* • Using the Canadian Occupational Performance Measure (COPM), participation goals are set with the patient within the first two weeks after admission. • The participation goals should be relevant both in the inpatient and home-based phase of the GR trajectory and regularly evaluated until the end of the GR treatment. • The participation goals should be easy to understand and made visible to the patients and their informal caregiver(s).
3)*Using eHealth to support rehabilitation* • Exploring the available eHealth options, such as video calling (e.g., via a tablet equipped with software specifically designed for individuals with little to no digital experiences), rehabilitation apps for home exercises (e.g. Physitrack, and activity monitoring using a wearable sensor to monitor daily movement, all aimed at supporting remote rehabilitation. • Assessing the skills of the patient regarding the available eHealth options and providing support and/or training if needed. • Early introduction and involvement of the patient and the informal caregiver(s) to the eHealth application(s) during the inpatient phase. Aim for continued use of eHealth during the home-based phase of the GR trajectory.
*4) Promoting patients’ self-management by applying Reablement strategies* • Enhancing self-management skills and strategies. • Involving the informal caregiver(s) during the GR trajectory and providing support where necessary. • Assess the patients’ social network and support the patient to activate the network if desired and/or needed. • Providing advice and/or training on the use of aids, devices and home adjustments. • Assess the local or regional social services and organized (leisure) activities and how these could support the patient by participating in meaningful activities in daily life.
*5)Close collaboration between all care partners involved during the GR trajectory* • Determine the provisional start date of home-based GR within the first two weeks after admission (if possible). • Prepare the patient and informal caregiver(s) and discuss possible barriers or limitations for home-based GR. • Timely organization of the necessary home care with (structural) agreements with the relevant formal caregivers (f.e. home care organizations, general practitioners, allied health professionals and/or medical specialists in secondary care). • Timely preparation of transfer to follow-up care.

### Data collection

Details of the data collection procedure for the cohort- and mixed method feasibility study are presented below. Details are provided separately in accordance with the aim of the Better@Home study, which is to assess the outcomes, costs, and feasibility of home-based GR after shorter inpatient rehabilitation.

#### Outcome assessment

The outcome assessment entails a *comparative evaluation* comparing the Better@Home cohort with a matched historical control group at GR admission and immediately post-GR, as well as a *follow-up evaluation* assessing the course of all outcomes between GR admission and three months of follow-up, solely in the Better@Home cohort. Table 2 presents the background characteristics, outcomes measured at each time point and the data collection methods for the prospective cohort study.

**Table 2 Tab2:** Background characteristics and outcome measures per time point

	Admission GR		Post GR		Follow-up 3 months
	**BH**	**CU**	**BH**	**CU**	**BH**
Patients					
*Outcome measures*					
Independence in daily functioning (BI)*	EPF	EPF	FI	EPF	FI
Performance in daily functioning (COPM-p)^#^	FI		FI		FI
Satisfaction with performance in daily functioning (COPM-s)	FI		FI		FI
Quality of life (EQ. 5D-5 L)	FI		FI		FI
B*ackground characteristics*					
Age	FI	EPF			
Sex	FI	EPF			
Educational level	FI				
Living arrangement	FI	EPF			
Diagnosis relevant for rehabilitation	RF	EPF			
Frailty (GFI)	FI				
Screening digital skills (Quick scan Pharos)	FI				
Informal caregivers					
*Outcome measure*					
Caregiver burden (CSI)	SQ		SQ		SQ
B*ackground characteristics*					
Age	SQ				
Sex	SQ				
Relationship to the patient	SQ				
Travel distance to the patient	SQ				

*BH* Better@Home cohort, *CU* Historical Control Group (care as usual), *EPF* Electronic Patient File, *FI *Face face-to-face interview patient, *RF* registration form care professionals, *SQ * structured questionnaire primary informal caregiver, *BI * Barthel-index, *COPM-p* Canadian Occupational Performance Measure-performance measure, *COPM-s * Canadian Occupational Performance Measure-satisfaction measure, *Eq. 5D* EuroQol health-related quality of life, *GFI* Groningen Frailty scale, *CSI* Caregiver Strain Index

*) Primary outcome measure comparative evaluation; ^#^) Primary outcome measure follow-up evaluation

#### Comparative evaluation

 The primary outcome measure for the *comparative evaluation* is independence in activities of daily living, assessed with the Barthel Index (BI) at admission to the GR facility and within two weeks post-GR, after completion of the GR trajectory. For both the Better@Home cohort and historical control group, the BI scores at admission are retrieved from the electronic patient files (EPF). The post-GR scores of the BI for the historical control group are also retrieved from the EPF. This data is routinely gathered by healthcare professionals of the participating GR facilities and stored in the EPF, most commonly in the Clinimetric Measurements tab. However, the post-GR scores of the BI for the Better@Home cohort are assessed by trained research assistants within 2 weeks of discharge. This is due to local GR protocols in which GR facilities do not routinely assess the BI after completion of home-based GR.

The BI, initially described by Mahoney and Barthel, is a 10-item measure of activities of daily living used in clinical practice to assess baseline abilities, quantify functional change after rehabilitation, and inform discharge planning. It comprises ten items: feeding, toilet use, bathing, grooming, dressing, bowel and bladder control, chair transfers, stair climbing, and ambulating [21]. In clinical practice, the patients are rated based on their medical records or direct observation. In a research setting, the patient is questioned during a face-to-face interview. Patients are rated on whether they can perform tasks independently, with assistance, or require assistance. The scoring on the modified version of the BI used in the present study ranges from 0 to 20. Higher scores indicate greater independence [21]. The BI’s structural validity, reliability, and interpretability are sufficient for measuring and interpreting changes in the physical function of geriatric rehabilitation patients [21–23].

In two of the participating facilities, the Utrecht Scale for Evaluation of Rehabilitation (USER) is used as an alternative for the BI [24, 25]. In these organizations, scores are converted from USER to BI [26]. This conversion is performed on a per-item level, as documented by DHU (De Hoogstraat Utrecht). For each BI-item, relevant scores on USER-items are matched, with the derived BI-item scores summed to the BI-total score. In the Netherlands, this conversion is common practice as GR facilities either use scores on the BI or the converted USER-scores to monitor progress in physical functioning.

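### Post-GR Barthel Index comes from a research interview in every Better@Home patient and from routine records in every control, so a measurement difference cannot be separated from the programme effect

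*Protocol article*

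**What the plan says.** The Comparative evaluation part of Outcome assessment (Protocol article, Data collection) defines the primary outcome as BI "assessed with the Barthel Index (BI) at admission to the GR facility and within two weeks post-GR, after completion of the GR trajectory". For both groups, "the BI scores at admission are retrieved from the electronic patient files (EPF"). For controls, "The post-GR scores of the BI for the historical control group are also retrieved from the EPF". For the programme cohort, "the post-GR scores of the BI for the Better@Home cohort are assessed by trained research assistants within 2 weeks of discharge". The stated reason is that "GR facilities do not routinely assess the BI after completion of home-based GR". Table 2 agrees: patient file in both groups at admission; post-GR, face-to-face interview for Better@Home and patient file for controls.

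The same section separates the two ways of scoring: "In clinical practice, the patients are rated based on their medical records or direct observation", whereas "In a research setting, the patient is questioned during a face-to-face interview".

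It adds that "In two of the participating facilities, the Utrecht Scale for Evaluation of Rehabilitation (USER) is used as an alternative for the BI", with file scores converted item by item to the BI.

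The primary model (Data analysis, Comparative evaluation) has group, time as a continuous variable, time by group and facility by group, with facility, age, sex, living situation and diagnosis as covariates. It has no term for mode or rater. The sensitivity analyses named under Cost assessment are a complete case analysis and a healthcare-perspective analysis. The limitations in the Discussion cover few outcomes and covariates, selection, non-randomisation and the lack of later control data.

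**The concern.** Three of the four group-by-time cells are professional scores taken from records. The fourth, Better@Home post-GR, is scored from questioning the patient, by study staff who necessarily know that every interviewee is in the programme. The programme cohort changes mode between its two measurements and the controls do not. If the two modes differ on average for the same patient at the same time, the difference looks like a programme effect or hides one.

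The primary result and the cost-effectiveness result are both at stake. The Cost assessment plan turns to cost minimisation if outcomes are comparable at lower cost, so a shift in favour of the programme could make a worse outcome look comparable. A shift the other way could make a useful programme look ineffective.

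**Working it through.** **1. Can the shift be separated from the effect?** Let D be the true programme effect and b the mean interview-minus-record difference in BI.

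| | Admission | Post-GR |
|---|---|---|
| Better@Home | record | interview (adds b) |
| Control | record | record |

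- Difference in post-GR BI, or in change from admission: D + b.
- With time continuous, a patient with trajectory length T has slope (true change + b)/T, so the time-by-group term moves by roughly b/T.
- Effect term of the ICER: D + b.

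Post-GR mode is collinear with group, and no patient is described as scored both ways. Covariates, facility dummies, frequency matching on admission BI and larger samples all leave b in place. The variance inflation factor (VIF) widens the variance; it does not remove a shift.

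**2. The plan's own figures.** Inputs from Setting and population: two-sided 5%, power 80%, VIF 2, 120:120 or 120:240.

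SE in SD units = sqrt(2 x (1/n1 + 1/n2)); detectable d = (1.960 + 0.842) x SE.

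- 120:120: SE = 0.183, d = 0.511 (stated 0.51).
- 120:240: SE = 0.158, d = 0.443 (stated 0.45).

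Both reproduce. Power at the stated d is 79.8% and 81.2%.

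**3. Illustration of size.** The documents give neither the BI SD nor b. Both are assumed here, in a simple comparison of two means and not in the planned slope model. With D = 0, P(significant) = 1 - Phi(1.96 - b/SE) + Phi(-1.96 - b/SE), with b in SD units. At 120:240:

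| Assumed SD | d = 0.45 in points | b = 0.5 point | b = 1 point | b = 2 points |
|---|---|---|---|---|
| 3 | 1.35 | 18.4% | 55.9% | 98.8% |
| 4 | 1.80 | 12.4% | 35.3% | 88.5% |
| 5 | 2.25 | 9.7% | 24.4% | 71.6% |

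Worked case: SD 4 and 1 point give b = 0.25 SD; 0.25/0.158 = 1.58; 1 - Phi(0.38) = 0.35. At 120:120 the same shift gives 27.8%.

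**4. Shift against the programme.** With true d = 0.45 at 120:240, power falls from 81% to 60%, 35% or 24% for an opposing shift of 0.10, 0.20 or 0.25 SD.

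**The case against.** The difference is disclosed and has a practical reason: on the article's account there is no routine end-of-trajectory score after home-based GR, so the interview fills a gap. The Discussion also warns that internal validity may be compromised. Both points are fair. But the reason given does not say how the difference will be handled, and the warning concerns confounding and selection. Measurement is a separate problem.

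The article also calls the BI adequate for measuring change. It does not say that interview and record scores are interchangeable.

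Four stronger readings are tempting, and the documents do not support them:

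- *The shift passes one-for-one into the primary effect.* That is true of a difference in post-GR BI or in change. The stated model has continuous time, so there the shift is scaled by trajectory length, which may differ between groups.
- *No analysis exists.* Only a condensed article is shown. It supports no more than that none is described here.
- *The two USER facilities mix instruments within Better@Home.* This is an inference, because the article does not say what the assistants use there. A difference in timing is likewise inferred: the two-week window is first stated without separating the groups.
- *The primary result is biased in favour of the programme, by a known amount.* The documents give no direction and no size. Nor is the interview bare self-report: a trained assistant questions the patient, and the patient is then rated.

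A further objection is that, for a simple mean difference, a tipping point only restates a confidence limit. That is correct, and it is why a plausible range must be set beforehand.

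**Conclusion.** The point holds as a differential-measurement problem that the article neither handles nor acknowledges. As data collection is described, no model fitted to these data can separate an interview-versus-record difference from the programme effect in the primary comparison, and the same difference enters the ICER. This rests on Table 2 and the accompanying text alone.

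The size is not known. The percentages show only that shifts smaller than the plan's own detectable difference would matter; they depend on the assumed SD (3 to 5), the assumed shift and the simple mean comparison. The shift could create or hide a difference. The sample size figures are not in dispute. The point should be acted on because the remedy is cheap and the primary contrast is hard to interpret without it.

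**What to change.** 1. Pre-specify a sensitivity analysis that refits the primary model and the ICER with Better@Home post-GR BI shifted by -2 to +2 points in steps of 0.5. Report the shift at which the conclusion changes.
2. State in advance, with reasons, the range of shifts considered plausible. Call the primary result robust only if it holds across that range.
3. Add differential measurement to the limitations in the Discussion.
4. State which instrument the assistants use in the two USER facilities. If it is the BI directly, repeat the analysis without those facilities.
5. A same-source comparison of record BI at the end of the inpatient phase, where recorded, may be added as supportive only.

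**Cost.** Items 1 to 3 need no new data. Item 4 loses the precision of two facilities and does nothing about mode in the other six. Item 5 needs one more field from the Better@Home files, which may not exist for all patients. It also measures the programme part-way, after a deliberately shortened inpatient stay, against controls at completion, so it answers a different question. Scoring a subsample by both modes would estimate the shift directly, but the article has data collection running only to April 2025, so that is probably no longer possible.
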